#### Randomization and blinding

A total of 340 participants will be randomly allocated into the treatment group or the control group. Each hospital will recruit 17 patients. In this trial, we will carry out block randomization in a 1:1 ratio according to the sequence generated using SAS software version 9.4 (SAS Institute Inc. Cary, NC). Random allocation will be performed after eligible participants consent in written form and complete baseline assessments. The central randomization system provided by the third party was used to generate the allocation sequence (http://zysj.clindacro.com/login.aspx), and the sub-center researchers (urologists) logged in the randomization system after screening the patients, input the account number and password, input the basic information of the subject according to the prompt, and the random system will give the subject code and random numbers. The sub-center therapists (acupuncturists) log into the central randomization system through their own account and password to check the subject codes, the random number, and treatment groups (acupuncture/non-meridian and non-acupoint shallow acupuncture). The participants, outcome assessors, and statisticians will be blinded to treatment allocation. The acupuncturist will not be blinded to the participant’s allocation. All participants in the study will sign a confidentiality commitment to avoid blind disclosure.

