#### Inclusion criteria

Patients who meet all the following requirements will be allowed to enroll:
Patients who have received radical prostatectomy with a definite pathological diagnosis of prostate cancer:Patients with urinary incontinence symptoms, which refer to the meaning of urinary incontinence by the International Continuity Society or evaluated by the urologists as experiencing urinary incontinence resulting from radical prostatectomy [23];Karnofsky Score ≥ 60 or Eastern Cooperative Oncology Group (ECOG) Score 0–2; andWilling to participate in the study and sign the consent forms.

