**Fig. 1 Fig1:**
[figure not shown]
Trial flowchart. UI, urinary incontinence; PC, prostate cancer; PPI, prostatectomy incontinence

**Table 1 Tab1:** Study design schedule

Contents	Research period								
	Screening	Baseline	Treatment (W1–6)				Follow-up (W7–24)		
	W−1	W0	W1	W2	W4	W6	W12	W18	W24
**Visit**	V0	V1	V2	V3	V4	V5	V6	V7	V8
**Name**	×	×							
**Age**	×	×							
**Contact information**	×								
**Inclusion/exclusion criteria**	×								
**Informed consent**	×								
**Screening dispose**	×								
**Randomization**	×								
**Vital signs**^**1**^	×	×	×	×	×	×			
**Blood routine**^**2**^	×	×				×			
**Urine routine**^**3**^	×	×				×			
**Biochemical items**^**4**^	×	×				×			
**ECG**^**5**^	×	×				×			
**Height**		×							
**Weight**		×							
**BMI**^**6**^		×							
**Education and occupation**		×							
**Karnofsky score**		×							
**ECOG score**^**7**^		×							
**Personal history**^**8**^		×							
**Past histories**		×							
**Physical examination**^**9**^		×	×	×	×	×			
**Diagnosis time**		×							
**Pathological type**		×							
**Gleason score**		×							
**Clinical stages**		×							
**Operation type**		×							
**Treatment of PPI**		×	×	×	×	×	×	×	×
**Treatment of PCa**		×	×	×	×	×	×	×	×
**Daily water consumption**		×	×	×	×	×	×	×	×
**Drink preference**		×	×	×	×	×	×	×	×
**Postoperative extubation time**		×							
**Time of incontinence**		×							
**ICIQ-UI SF**^**10**^		×				×	×	×	×
**1-h pad test**		×			×	×			
**72-h voiding diary**		×	×	×	×	×	×	×	×
**EPIC-26**^**11**^		×				×	×	×	×
**SAS**^**12**^		×				×	×	×	×
**Weekly consumption of pads**		×	×	×	×	×	×	×	×
**Severity of PPI**		×				×	×	×	×
**Self-assessment**						×	×	×	×
**Blind assessment**						×			
**Major AE of PCa**^**13**^			×	×	×	×	×	×	×
**AE**^**14**^			×	×	×	×	×	×	×
**SAE**^**15**^			×	×	×	×	×	×	×

Notes:

^1^Vital signs: blood pressure, pulse, body temperature, and respiration

^2^Blood routine: hemoglobin, red blood cell count, white blood cell count, lymphocyte, neutrophil, and platelet count

^3^Urine routine: white blood cell, red blood cell, protein, and ketone body

^4^Biochemical items: alkaline phosphatase, alanine aminotransferase (ALT), aspartate aminotransferase (AST), total bilirubin, urea nitrogen, glomerular filtration rate, creatinine, glucose, triglyceride, total cholesterol, high-density lipoprotein, low-density lipoprotein, potassium, sodium, calcium

^5^ECG: electrocardiogram

^6^BMI: body mass index

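### Table 1 schedules randomisation at screening (V0, W−1), one visit before the baseline ICIQ-UI SF at V1 (W0), contrary to the text's rule that allocation follows baseline assessment

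*Protocol article*

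**What the plan says.** **Text.** Randomization and blinding gives the order explicitly: "Random allocation will be performed after eligible participants consent in written form and complete baseline assessments". The same section says that the urologist logs in to the central system once the patient has been screened. It also says that the acupuncturist can look up the treatment group under a separate account. Participants, outcome assessors and statisticians are blinded; the acupuncturist is not.

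**Schedule.** The week labels of Table 1 run "W−1 W0 W1 W2 W4 W6 W12 W18 W24". The first column is Screening (V0) and the second is Baseline (V1). The row "Randomization" has a single mark, under Screening. The row "Inclusion/exclusion criteria" is also marked only there. The ICIQ-UI SF is first marked under Baseline. The rows "Karnofsky score", "Pathological type" and "Past histories" are marked under Baseline only.

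**Eligibility.** The Inclusion criteria require "Karnofsky Score ≥ 60 or Eastern Cooperative Oncology Group (ECOG) Score 0–2", and also a definite pathological diagnosis. Several Exclusion criteria rest on medical history.

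**Primary outcome.** The Abstract defines it as the change in ICIQ-UI-SF from baseline to week 6, and Sample size calculation is built on the between-group difference in that reduction.

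**The concern.** Both orders cannot hold. The text puts the baseline first and allocation second; the table puts allocation at one visit and the baseline at the next. The schedule of visits is what site staff work from day to day, and 20 hospitals are to follow it.

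Three things are at stake if a site follows the table:

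- The baseline half of the change score is collected after allocation, so the order of events no longer guarantees that it is independent of the arm.
- A man who leaves between W−1 and W0 is already randomised but has no baseline value for the primary outcome.
- Performance status, pathology and history are recorded only after allocation. If an entry contradicts the eligibility check made at screening, the discrepancy comes to light in a man who is already randomised.

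**Working it through.** **1. The plan's own figure.** The sample size was reproduced first, to see whether it bears on the point. Inputs from Sample size calculation: difference 2.5, SD 6.3, two-sided alpha 0.05, power 90%, dropout 20%.

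- n per arm = 2 × (1.960 + 1.282)² × 6.3² / 2.5² = 133.4, rounded up to 134.
- Allowing for dropout: 134 / 0.80 = 167.5, rounded up to 168 per arm, or 336 in total, against 340 stated.
- With 170 × 0.80 = 136 evaluable men per arm, power is 0.905.

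The figure reproduces and is unaffected. The point concerns the order of events.

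**2. Table 1, row by row.**

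| Row | Screening (V0, W−1) | Baseline (V1, W0) |
|---|---|---|
| Informed consent | × | |
| Inclusion/exclusion check | × | |
| Randomisation | × | |
| Vital signs, blood, urine, biochemistry, ECG | × | × |
| Karnofsky, ECOG | | × |
| Pathological type, past histories | | × |
| ICIQ-UI SF | | × |
| 1-h pad test, 72-h diary, EPIC-26, SAS, weekly pads, severity | | × |

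Every efficacy measure that has a baseline gets its first mark one column after randomisation.

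**3. Could this be a fault in reading the table?** It is unlikely. Rows marked only at baseline, such as height, have an empty first cell; the randomisation row does not. Rows marked at several visits, such as vital signs, fall in the expected columns (W−1, W0, W1, W2, W4, W6).

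**4. Does other text settle the order?** It does not.

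- Baseline assessment says only that baseline registration comes before treatment. Either order satisfies that.
- The log-in after screening, in Randomization and blinding, is compatible with the table's order.
- Safety assessment places the laboratory tests and ECG before randomisation. Table 1 marks them at both visits, so they fit either order.
- Fig. 1 is not available in the text reviewed.

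**5. What follows if the table is obeyed.** Let D be the between-group difference in mean change:

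D = (week 6 − baseline) in the acupuncture arm − (week 6 − baseline) in the sham arm.

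If knowledge of allocation moved the mean baseline score of one arm by b points, D would move by b points in absolute value. The documents give no value or range for b, so none is put in. A man who withdraws between V0 and V1 has neither end of the change score, and the multiple imputation named under Statistical analysis would have to supply both.

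**The case against.** The strongest reply is that the governing rule in the text is already sound and that one mark in a summary table disagrees with it. That is fair as to which statement should prevail. It does not remove the conflict, because the log-in after screening leaves a site able to follow the table and think itself compliant.

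Three stronger readings are tempting, and the documents do not support them.

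- **That the baseline would be biased, by some stated share of the 2.5-point target.** At W0 the participant is blinded and untreated, and outcome assessors are blinded. The urologist is described as receiving a subject code and random number; it is the acupuncturist who sees the group. Nothing says that the acupuncturist collects baseline scores. An arm-specific shift, or arm-specific withdrawal, would need information to leak before the first session. That is a residual risk, and any figure for it would be invented.
- **That the schedule prescribes randomising men of unknown eligibility.** The inclusion/exclusion check is marked at W−1, as are the laboratory tests and ECG that bear on several exclusions. The Karnofsky, ECOG and history rows at W0 may only document criteria already checked. What remains is the possibility that an entry at W0 contradicts the earlier check.
- **That the randomisation system fails to require baseline data before it releases an allocation.** The article says only that basic information is entered as prompted. Such detail is commonly left to the full protocol, so its absence here shows nothing.

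**Conclusion.** The contradiction stands: Table 1 puts allocation one visit before the baseline of the primary outcome and before all the other efficacy baselines, and the text requires the reverse. It should be corrected, because it concerns the baseline of a change-from-baseline primary outcome and the schedule is an operational document for 20 sites.

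The consequence is conditional. It arises only at sites that follow the table rather than the text. There, the baseline would be recorded when the unblinded acupuncturist can already see the arm, and some randomised men could lack a baseline ICIQ-UI SF or prove to conflict with the eligibility check. Blinding of participants and assessors limits the likely bias. The documents support no estimate of its size, nor of how many men would be affected, and the sample size does not change. The conclusion assumes that the columns of Table 1 were read correctly, as the neighbouring rows indicate.

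**What to change.** In Table 1, remove the randomisation mark from V0 (W−1) and place it at V1 (W0). Add a note that allocation is requested only after the ICIQ-UI SF, the other baseline measures and the eligibility items recorded at that visit are complete. This brings the schedule into line with the rule already in Randomization and blinding. In that section, the reference to logging in after screening could be extended to say after screening and baseline assessment. Send the correction to all sites.

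The cost is a table correction and a site notice, with no extra visits or measurements and no change to the sample size. For men already enrolled, comparing the date of allocation with the date of the baseline ICIQ-UI SF would show whether any site had followed the table.

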#### Ethics

The study will be performed in accordance with the principles of the Declaration of Helsinki and has been approved by the ethics committee boards of the participating hospitals. Written informed consent will be obtained from each subject before the patients are enrolled in the trial.

### Interventions

According to the predetermined randomization results, participants will be randomly allocated to the verum or sham acupuncture group. All participants will go through a standardized interview, which will be recorded on the case report forms. To minimize bias, all the acupuncturists in this trial are specialists in acupuncture. They have a minimum of 2 years experience in acupuncture treatment and hold licenses to perform acupuncture. Before performing this trial, all acupuncturists will receive special training regarding the purpose and content of the trial, treatment strategies, and quality control. The flowchart and study design schedule are presented in Fig. 1 and Table 1, respectively.

**Fig. 1 Fig1:**
[figure not shown]
Trial flowchart. UI, urinary incontinence; PC, prostate cancer; PPI, prostatectomy incontinence

**Table 1 Tab1:** Study design schedule

Contents	Research period								
	Screening	Baseline	Treatment (W1–6)				Follow-up (W7–24)		
	W−1	W0	W1	W2	W4	W6	W12	W18	W24
**Visit**	V0	V1	V2	V3	V4	V5	V6	V7	V8
**Name**	×	×							
**Age**	×	×							
**Contact information**	×								
**Inclusion/exclusion criteria**	×								
**Informed consent**	×								
**Screening dispose**	×								
**Randomization**	×								
**Vital signs**^**1**^	×	×	×	×	×	×			
**Blood routine**^**2**^	×	×				×			
**Urine routine**^**3**^	×	×				×			
**Biochemical items**^**4**^	×	×				×			
**ECG**^**5**^	×	×				×			
**Height**		×							
**Weight**		×							
**BMI**^**6**^		×							
**Education and occupation**		×							
**Karnofsky score**		×							
**ECOG score**^**7**^		×							
**Personal history**^**8**^		×							
**Past histories**		×							
**Physical examination**^**9**^		×	×	×	×	×			
**Diagnosis time**		×							
**Pathological type**		×							
**Gleason score**		×							
**Clinical stages**		×							
**Operation type**		×							
**Treatment of PPI**		×	×	×	×	×	×	×	×
**Treatment of PCa**		×	×	×	×	×	×	×	×
**Daily water consumption**		×	×	×	×	×	×	×	×
**Drink preference**		×	×	×	×	×	×	×	×
**Postoperative extubation time**		×							
**Time of incontinence**		×							
**ICIQ-UI SF**^**10**^		×				×	×	×	×
**1-h pad test**		×			×	×			
**72-h voiding diary**		×	×	×	×	×	×	×	×
**EPIC-26**^**11**^		×				×	×	×	×
**SAS**^**12**^		×				×	×	×	×
**Weekly consumption of pads**		×	×	×	×	×	×	×	×
**Severity of PPI**		×				×	×	×	×
**Self-assessment**						×	×	×	×
**Blind assessment**						×			
**Major AE of PCa**^**13**^			×	×	×	×	×	×	×
**AE**^**14**^			×	×	×	×	×	×	×
**SAE**^**15**^			×	×	×	×	×	×	×

Notes:

^1^Vital signs: blood pressure, pulse, body temperature, and respiration

^2^Blood routine: hemoglobin, red blood cell count, white blood cell count, lymphocyte, neutrophil, and platelet count

^3^Urine routine: white blood cell, red blood cell, protein, and ketone body

^4^Biochemical items: alkaline phosphatase, alanine aminotransferase (ALT), aspartate aminotransferase (AST), total bilirubin, urea nitrogen, glomerular filtration rate, creatinine, glucose, triglyceride, total cholesterol, high-density lipoprotein, low-density lipoprotein, potassium, sodium, calcium

^5^ECG: electrocardiogram

^6^BMI: body mass index

^7^ECOG score: Eastern Cooperative Oncology Group score

^8^Personal history: including family history, smoking history, drinking history, drug and food allergy history, marriage history, occupational exposure history

^9^Physical examination: the researchers will conduct a comprehensive physical examination at baseline, including general appearance, skin, neck (including thyroid), eyes, ears, nose, throat, lung, heart, abdomen, back, lymph nodes, limbs, and nervous system examination. All other visits will have a brief physical examination, i.e., a general appearance examination

^10^ICIQ-UI SF: International Consultation Incontinence Questionnaire-Urinary Incontinence Short Form

^11^EPIC-26: The Expanded Prostate Cancer Index Composite 26-item version

^12^SAS: Self-Rating Anxiety Scale is a 20-item self-report assessment

^13^Major adverse event (AE) of prostate cancer (PCa): it refers to the AEs related to the progression of PCa from the time of enrollment to the end of follow-up

^14^AE: It refers to the AEs caused by the intervention measures of the project from the time of admission to the end of follow-up

^15^SAE: It refers to the serious adverse events caused by the intervention measures of the project during the period from enrollment to the end of follow-up

The trial will last 24 weeks, including treatment and follow-up periods. All participants will receive treatment for 6 weeks. Participants in both groups will receive verum or sham acupuncture three times a week (recommended interval of one day). Each acupuncture session requires approximately 20 min to perform. Sterile needles for single use (0.25 × 40 mm; Jiangsu Medical Supplies Factory Co., Ltd.) will be used in this study. Needles in the treatment group will be inserted at a depth of 0.8-1 inches and manually manipulated by rotation methods. After acupuncture, the patient's "De Qi" should be taken as the criterion (the feeling of pain and numbness). In the control group, needles will be inserted about 0.5 inch in depth and will not receive further manipulation. To prevent blind uncovering, the operator will pay attention to the depth and angle of the shallow stab. All participants will be evaluated by blind method at week 6 after acupuncture. The Blind Method Assessment is shown in Additional file 1.

All participants need to stay in the hospital for observation for at least 10 min after acupuncture, and can leave only with no discomfort.

In order to ensure the safety of participants, in case of emergency events, it is necessary to break the blindness in advance if there is any adverse event which could not be judged whether it is related to acupuncture intervention. When the blinding is broken, the time, reason, and personnel performing the blind breaking ahead of time shall be recorded and the supervisor shall be notified in time. Once the blinding is broken, the patient would not continue to participate in the study, and the tested data should not be adopted in this study. However, the safety analysis data should still be included.

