#### Statistical analysis

Summary tables (descriptive statistics and/or frequency tables) will be provided for all variables as appropriate. The primary outcome analysis will use the Cochran-Mantel-Haenszel (CMH) test. For continuous variables, means and standard deviations will be presented, unless the variable has a skewed distribution, in which medians, 25th and 75th percentiles will be presented. For other categorical data, between-group comparisons will be performed using a Wilcoxon rank-sum test, chi-square test, or Fisher’s exact test, as appropriate. AE incidences for each treatment group will be tested by the *χ*^2^ test or Fisher’s exact test as appropriate. All the statistical analysis will be performed using SAS version 9.4 (SAS Institute Inc) with 2-sided tests at a significance level of < 0.05. We will use the multiple imputation to handle missing data.

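### Table 1 notes 14 and 15 define AEs and SAEs as intervention-caused events only; this conflicts with the protocol's wider use of the term and makes the between-arm AE test depend on a causality judgement

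*Protocol article*

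**What the plan says.** Table 1 has three event rows, each marked at every visit from W1 to W24, and its notes define them.

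- Note 13, major AE of prostate cancer: "it refers to the AEs related to the progression of PCa from the time of enrollment to the end of follow-up". No link to the intervention is required.
- Note 14, AE: "It refers to the AEs caused by the intervention measures of the project", with the period running from admission until follow-up ends.
- Note 15, SAE: "It refers to the serious adverse events caused by the intervention measures of the project during the period from enrollment to the end of follow-up".

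On analysis, the Statistical analysis section says "AE incidences for each treatment group will be tested by the" chi-square or Fisher's exact test.

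Three other places use the term without the causal condition. The Interventions section says that in an emergency "it is necessary to break the blindness in advance if there is any adverse event which could not be judged whether it is related to" the needling, and it keeps the safety data after the blind is broken. The Safety assessment section speaks of any AE arising during the trial. The Adverse events section lists common treatment-related AEs as one kind of AE.

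On blinding, the Randomization and blinding section says: "The acupuncturist will not be blinded to the participant’s allocation". Participants, outcome assessors and statisticians are blinded.

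**The concern.** Safety is a stated objective and the arms are to be compared on AE incidence. Randomization protects a comparison of all events. It does not protect a comparison of events that someone has decided were caused by treatment, because that decision comes after allocation and can differ by arm. Notes 14 and 15 make cause part of the definition instead of a separate attribute of a recorded event.

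Two things are at stake. First, the AE comparison can show a difference that is not there, or miss one that is. Second, an unexpected harm is often not recognised as caused by treatment when it occurs. Under these definitions a hospitalisation or cardiac event attributed neither to needling nor to cancer progression has no event row. With 20 hospitals, the conflicting uses of the term also leave room for sites to collect different things.

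**Working it through.** **1. The texts side by side.**

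| Place | Meaning of adverse event | Cause required? |
|---|---|---|
| Table 1 note 13 | Linked to cancer progression | Not the intervention |
| Table 1 note 14 | AE row, W1 to W24 | Yes, the intervention |
| Table 1 note 15 | SAE row, W1 to W24 | Yes, the intervention |
| Interventions, emergency unblinding | Relatedness cannot be judged | No |
| Safety assessment | Any AE in the trial | No |
| Adverse events | Treatment-related AEs are a subset | No |

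If treatment-related AEs are a subset, AEs that are not treatment-related must exist, yet notes 14 and 15 give them no row. An event whose relatedness cannot be judged is called an adverse event under Interventions but does not meet note 14 until someone attributes it. The two sets of passages cannot both define what the Statistical analysis section counts.

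**2. Who judges cause.** No passage says. The acupuncturist knows the arm. The Adverse events section leaves decisions on continued participation to researchers and the investigator, and the randomization text identifies the sub-center researchers as urologists. They receive a subject code and random number, while the therapists are the ones described as checking the treatment group. Urologists are not listed as blinded unless they are the outcome assessors. In an emergency with unclear relatedness the blind is broken, so attribution may then be made with the arm known.

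**3. The plan's own figure.** The AE analysis has no stated rate or power. The only figure with inputs is the sample size (difference 2.5, SD 6.3, two-sided alpha 0.05, power 90%, dropout 20%).

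- n per arm = 2 × [6.3 × (1.960 + 1.282) / 2.5]² = 133.5, rounded up to 134.
- 134 / 0.8 = 167.5, rounded up to 168 per arm, 336 in total against the stated 340.
- With 170 × 0.8 = 136 completers per arm, SE = 6.3 × √(2/136) = 0.764. Power = Φ(2.5/0.764 − 1.960) = 0.905.

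The figure reproduces and does not depend on the AE definition.

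**4. Illustration (all rates assumed).** Let p be the true share of participants with an event and a the share of those attributed to the intervention. The counted rate is q = p × a. With n = 170 per arm, the chance of a significant result is Φ[(|q₁ − q₀| − 1.960 × SE₀) / SE₁], where SE₀ = √(2q̄(1 − q̄)/n), q̄ is the mean of q₁ and q₀, and SE₁ = √([q₁(1 − q₁) + q₀(1 − q₀)]/n).

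| True rates | Attributed | Counted rates | Chance of significance |
|---|---|---|---|
| 20% vs 20% | 80% vs 80% | 16% vs 16% | no distortion of the null |
| 20% vs 20% | 80% vs 40% | 16% vs 8% | 62% (spurious) |
| 20% vs 10% | 100% vs 100% | 20% vs 10% | 74% |
| 20% vs 10% | 50% vs 50% | 10% vs 5% | 42% |
| 20% vs 10% | 40% vs 80% | 8% vs 8% | real difference hidden |

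Second row: SE₀ = 0.0352, SE₁ = 0.0350, and (0.08 − 1.960 × 0.0352)/0.0350 = 0.31, so Φ = 0.62.

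With rarer events the reported counts are still distorted but need not reach significance. If 10 events per arm were attributed 50% in one arm and 10% in the other, the report would show 5 against 1, with Fisher's exact p = 0.21 at 170 per arm.

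**The case against.** The best defence is that this is a condensed article. Relatedness categories, case report form fields and reporting procedures normally sit in the full protocol, which is not shown, and the wider uses of the term suggest that sites may record more than the notes say. Part of this stands: silence on procedure is no defect here. But notes 14 and 15 are not silent. They state a definition, and it conflicts with the text around it.

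Several stronger readings are tempting, and the documents do not support them.

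- *Events judged unrelated are never counted.* Note 13 captures cancer-progression events whatever their cause, safety data are kept after emergency unblinding, and laboratory tests and ECG are repeated at week 6 for everyone. Those tests do not replace event reporting and are not scheduled after week 6, but the word never goes too far.
- *Unblinded staff make the attribution.* The acupuncturist is unblinded, but no passage gives that person the causality judgement, and the Adverse events section points to researchers and the investigator.
- *The judgement comes before an event is recorded.* This is inferred from the definition. No passage gives the order of recording and attribution.
- *The data and safety monitoring committee would not see unattributed serious events.* The Quality control section says that it evaluates safety indicators and does not tie these to notes 14 and 15.
- *Attribution will differ between real and sham needling.* This is plausible, since the sham points are described as having no therapeutic value, but it is not documented.

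**Conclusion.** The point holds as a defect in stated definitions. Notes 14 and 15 restrict the scheduled AE and SAE items to intervention-caused events, with cancer progression as the only other event row. This contradicts three other sections, and the AE test, followed as written, rests on a causality judgement by an unspecified person who may know the allocation.

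The documents do not fix its size. Under the assumed rates, the effect runs from none (equal attribution, no true difference), through a loss of power from 74% to 42% (equal 50% attribution of a real difference), to a 62% chance of a spurious finding or complete masking (unequal attribution). These figures assume 170 analysed per arm, at most one counted event per participant and a normal-approximation test. The primary efficacy analysis and the sample size are untouched. The change should be made, because the safety comparison as defined is not reliable.

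**What to change.** 1. Rewrite notes 14 and 15 so that an AE is any untoward medical event in the stated period regardless of cause, and an SAE is any such event that is serious. The two notes describe the start of the period differently (admission and enrollment), so use one term. Note 13 can remain as a category within this.
2. Reconcile the use of the term in the Interventions, Safety assessment and Adverse events sections with the new definition. This concerns terminology only; the rules on unblinding and on continued participation are not at issue here.
3. Record relatedness as a separate field for every event, with a category for relatedness that cannot be judged. Name who completes it, using existing blinded staff where possible, and note whether the blind had already been broken.
4. In the Statistical analysis section, compare all-cause AE and SAE incidence by arm first, then treatment-related incidence.

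The cost is protocol and case report form wording, retraining at 20 sites, and somewhat more AE entry at visits where AEs are already scheduled. No extra visits or participants are needed. For participants already enrolled, sites would have to check source records for events left out under the narrower definition.

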## Methods

### Study design

This study is a multicenter, single-blind, randomized parallel controlled prospective clinical trial with the objective of estimating the efficacy and safety of acupuncture on PPI by comparing a verum acupuncture group with a sham acupuncture group. Participants considered suitable for the study will be randomly allocated into the intervention group (verum acupuncture) or the control group (sham acupuncture) in a 1:1 ratio. This is a clinical trial of superiority.

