### Adverse events

With any adverse events during treatment, protective therapeutic measures shall be taken in time to ensure the safety of participants. According to the different levels of adverse events, researchers will make the judgment if the participants will continue, suspend, or withdrawal from the study. Common treatment-related AEs including fainting during acupuncture, local bleeding, sticking of needle, subcutaneous hematoma, and itching at the sites of needle insertion. If the patient has an adverse event due to acupuncture and the investigator decided that the patient would not suitable to continue to participate the trial, the patient will be weeded out consequently.

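### Emergency unblinding ends participation and excludes the participant's non-safety data, a post-randomisation exclusion that may depend on arm and outcome

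*Protocol article*

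**What the plan says.** The rule stands in the Interventions section of the protocol article, after the notes to Table 1. It sets the trigger first: in an emergency, "it is necessary to break the blindness in advance if there is any adverse event which could not be judged whether it is related" to the acupuncture. Once blinding is broken, "the patient would not continue to participate in the study, and the tested data should not be adopted in this study". The next sentence makes the only exception: "However, the safety analysis data should still be included". Because safety data alone are kept, the natural reading is that the efficacy data are set aside.

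The Adverse events section has a second route out of the trial. If an acupuncture-related event leads the investigator to judge a participant unsuitable to continue, "the patient will be weeded out consequently". What happens to that participant's data is not stated.

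The Statistical analysis section says "We will use the multiple imputation to handle missing data". It names no analysis set, and it does not say whether imputation covers unblinded participants. Under Study design the article states "This is a clinical trial of superiority", and Randomization and blinding specifies "block randomization in a 1:1 ratio".

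**The concern.** A randomised comparison is protected only while everyone allocated stays in the analysis of the arm to which they were allocated. This rule removes participants because of something that happens after allocation.

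The event could be linked to arm, because the needling differs. Verum needles are "inserted at a depth of 0.8-1 inches and manually manipulated by rotation methods", while sham needles go in about 0.5 inch and are not manipulated. It could also be linked to outcome, if men who have such events improve more or less than the others. If both links hold, the groups that remain are no longer the groups that were randomised, and a superiority test can be shifted in either direction. Even without bias, information that has been collected, or could have been, is lost.

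**Working it through.** **What is lost, by time of unblinding.** Table 1 schedules the ICIQ-UI-SF at baseline and weeks 6, 12, 18 and 24. The voiding diary and pad count are at baseline and weeks 1, 2, 4, 6, 12, 18 and 24, and the pad test at baseline and weeks 4 and 6. Adverse events are recorded from week 1 to week 24, so unblinding can arise at any point in that span.

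| Unblinding | Primary outcome (week-6 change) | Secondary outcomes |
|---|---|---|
| Before the week-6 visit | No post-baseline score exists yet; the score becomes missing because participation ends | Diary, pad count and pad test already observed are discarded; later ones are not collected |
| Weeks 7 to 24 | The week-6 score, observed while blinded, is discarded | All observed values are discarded; later ones are not collected |

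**The plan's own figure.** Inputs from Sample size calculation: difference 2.5, SD 6.3, two-sided alpha 0.05, power 90%, dropout 20%.

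- n per arm = 2 × (1.960 + 1.282)² × 6.3² / 2.5² = 133.5, rounded up to 134.
- With dropout, 134 / 0.80 = 167.5, rounded up to 168 per arm, 336 in total.
- The stated 340 (170 per arm) is therefore reproduced. It leaves 170 × 0.80 = 136 evaluable per arm, with power 90.5%.

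The sample size is sound and is not the issue.

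**Shift in the estimated difference.** Let f be the fraction of an arm removed, and D the amount by which those removed improve less than those kept. The mean of those kept exceeds the mean of the whole arm by f × D. With the same D in both arms, the difference shifts by (f_verum − f_sham) × D. The article gives neither f nor D, so every row is an assumption.

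| Removed, verum vs sham | D (points) | Shift (points) | Share of 2.5 |
|---|---|---|---|
| 2% vs 0% | 2.5 | 0.02 × 2.5 = 0.05 | 2% |
| 5% vs 1% | 2.5 | 0.04 × 2.5 = 0.10 | 4% |
| 5% vs 1% | 5 | 0.04 × 5 = 0.20 | 8% |
| 8% vs 2% | 2 to 4 | 0.06 × D = 0.12 to 0.24 | 5% to 10% |
| 15% vs 5% | 2 to 4 | 0.10 × D = 0.20 to 0.40 | 8% to 16% |
| 10% vs 2% | 5 | 0.08 × 5 = 0.40 | 16% |
| 5% vs 5% | any, same in both arms | 0 | 0% |

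In head counts, two verum men and no sham men removed, each with a 4-point shortfall, gives 2/170 × 4 = 0.05 points. If those removed improve more than the others, D is negative and the sign of the shift reverses.

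**Error rates.** Assume no true effect and 136 evaluable per arm before exclusion. With SE = 6.3 × √(1/n_verum + 1/n_sham), the two-sided type I error is 1 − Φ(1.96 − shift/SE) + Φ(−1.96 − shift/SE).

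- 5% vs 1%, D = 5: n = 129.2 and 134.6, SE = 0.776, shift/SE = 0.26, type I error about 5.8%.
- 10% vs 2%, D = 5: n = 122.4 and 133.3, SE = 0.789, shift/SE = 0.51, type I error about 8.0%.

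If exclusions come on top of the 20% dropout and are equal in both arms, power falls from 90.5% to 90.0% at 2%, 89.1% at 5% and 87.4% at 10%.

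**The case against.** The strongest case against has four parts.

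1. *The trigger is narrow.* A reader might infer that men are excluded for treatment-related events. The rule covers emergencies whose cause cannot be judged. The common needling events listed under Adverse events (fainting, bleeding, stuck needle, haematoma, itching) can usually be attributed without unblinding, and they are the ones most likely to vary with depth and manipulation. This stands: an imbalance between arms is possible, but the article gives no figure from which to expect one.

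2. *Before week 6 there is no post-baseline primary score to delete.* A reader might infer that the rule mainly erases observed primary outcomes. For unblinding during treatment it creates a missing value, to which multiple imputation could be applied. This also stands. But the article does not say that imputation covers these men, and imputation is no reason to discard values that were observed.

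3. *Direction and rates are assumed.* A reader might infer that the rule favours verum. That needs both more removals in the verum arm and poorer improvement among those removed, and the documents support neither. The Background describes acupuncture as having few adverse effects. On 170 men, 8% is about 14 and 15% about 26, which would be many emergency unblindings in one arm.

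4. *Analysis sets are commonly left to the SAP, which is not shown.* True, and the absence of a named set is no fault in an article. But this is an explicit instruction, not a silence. A SAP that kept these data would contradict the protocol, and one that followed the protocol would carry the exclusion through.

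**Conclusion.** The point holds as a stated post-randomisation exclusion. The rule discards observed secondary data, discards an observed week-6 primary score when unblinding falls in weeks 7 to 24, and otherwise creates a missing one. Nothing in the article overrides it.

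The size and direction of bias are unknown. The shift is about 0.05 points if unblinding is rare and 0.1 to 0.4 points at the higher assumed rates, against the 2.5-point target. It is zero if removal and shortfall are equal in both arms. These figures assume a common shortfall in both arms and removal fractions that the article does not give. That the set-aside data are the efficacy data is inferred from the exception made for safety data.

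The documents do not support saying that the trigger is an established treatment effect, that the rule favours verum, or that the primary comparison is seriously distorted. The case for correcting it is that its effect cannot be known in advance, and that a trial following it literally could not report all randomised participants.

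**What to change.** Replace the data-exclusion clause in the emergency-unblinding paragraph with:

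> All randomised participants, including those unblinded, are analysed in the group to which they were randomised. All data collected are retained, and scheduled outcome questionnaires continue to be sought where consent allows. A sensitivity analysis excludes data collected after unblinding.

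State the same retention rule in the Adverse events section for participants removed there, and carry both into the SAP before the database is locked. Whether study treatment continues after unblinding or an adverse event is a separate clinical decision, which this change leaves alone.

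The cost is a few sentences and some continued questionnaire follow-up. The sensitivity analysis is feasible because the rule already requires the time of unblinding to be recorded. The one downside is that some self-reports given after unblinding may be influenced by knowledge of the allocation, and the sensitivity analysis addresses that.
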